### Plans to promote participant retention and complete follow-up {18b}

Due to the nature of terminal delirium, patients’ prognoses are short, and they may become deceased before completing all time points in the study. As such, daily visits and assessments by the investigators will be conducted. This serves to ensure compliance with the intervention, completeness of data collection, as well as allow the clinicians to render support for the family where needed.

In the event the patient dies before the final assessment, the investigators will still make a final home visit to make a final assessment with the caregivers, and to collect the case report form and remaining medication. The family will continue to receive psychosocial support from their palliative care provider, including subsequent bereavement support.

### Data management {19}

Each trial will have an associated case report form, which will be reviewed by the visiting investigator after each visit to ensure the accuracy of recorded data.

Data will initially be recorded on hardcopies of the case report forms by both the clinician and caregiver before they are transcribed to a Microsoft Excel file. The file is web-based and access-secured; only the investigators are able to access the file via their hospice organizational account. For electronic data, they will be stored in an encrypted and password-protected excel file. At the completion of data collection and initiation of analysis, participant identifiers will be removed from the file. The de-identified file will remain while the file with participant identifiers will be destroyed

For hardcopy data, they will be stored in designated locked cabinet(s) or room(s) that are accessible to authorized study personnel only. Only the patient’s Trial Identification Number will be used to identify the hardcopy.

Records for all participants, including case report forms, all source documentation (containing evidence to study eligibility, history and physical findings, laboratory data, results of consultations, etc.) as well as Institutional Review Board (IRB) records and other regulatory documentation should be retained by the PI in a secure storage facility. The records should be accessible for inspection and copying by authorised authorities.

### Confidentiality {27}

The electronic file will contain only de-identified data and will be stored in a secure folder in the hospice intranet which is only accessible to research staff. Hardcopy data will be stored up to 2 years after the publication of the study. At the end of two years, the hardcopy will be shredded and disposed of in accordance with MOH’s guidelines for personal and sensitive information.

The patient’s Hospice Identification number (known as the HAH number) will be collected for the purposes of extracting demographic information from the electronic medical records. Demographic data, including age, sex, and primary diagnoses, will be extracted for descriptive presentation.

### Plans for collection, laboratory evaluation and storage of biological specimens for genetic or molecular analysis in this trial/future use {33}

Not applicable.

## Statistical methods

### Statistical methods for primary and secondary outcomes {20a}

For the first primary outcome, changes to the severity of delirium over three 24-h periods, as measured with the MDAS, would be analysed using repeated-measures, between-factors ANOVA. If a statistically significant difference is found between medications, post hoc analysis will be conducted to analyse the change in MDAS scores at each time-point.

The second outcome, changes in the patient’s agitation, will be measured using the RASS score. Similarly, the repeated-measures, between-factors ANOVA would be used to analyse the differences in scores.

Additional outcomes of interest are possible toxicity effects due to the medication, which is measured using NCI CTCAE. For each group, the frequency of toxicities (Akathisia, Extrapyramidal disorder, and spasticity) for each group will be compared.

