### Outcomes {12}

The primary outcome is the reduction in delirium severity as measured with the Memorial Delirium Assessment Scale (MDAS). Secondary outcomes are the reduction in the severity of agitation as measured with the Richmond Agitation-Sedation Scale modified for palliative care (RASS), and the frequency and severity of medication toxicities, as measured using the National Cancer Institute Common Terminology Criteria for Adverse Events (NCI-CTCAE). These data will be collected over four time-points: (i) baseline, (ii) 24 h after commencement, (iii) 48 h after commencement, and (iv) 72 h after commencement.

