### Sample size {14}

Based on validation studies by Breitbart et al. [13] and Lawlor et al. [14], the mean scores from the Memorial Delirium Assessment Scale for patients with delirium is roughly 18 (SD = 7.64). Jain et al. [10] reported that using either haloperidol or olanzapine led to a nearly 55% reduction in patients’ MDAS score (7–8 points). Based on this, we estimate 2 points to be the minimal important difference between haloperidol and olanzapine; a 2-point difference between the treatment arms is equivalent to a 25% difference in the reduction of a patient’s MDAS score. Table 3 details sample size calculations, using the parameters as presented above.

**Table 3 Tab3:** Sample size calculation for repeated measures design

Sample size calculation for repeated measures design	
Standard deviation (drawn from literature review)	7.64
Estimated minimal important difference (effect size)	2
Target power (1-β error probability)	.80
Target *alpha*	.05
Estimated required size per treatment arm	32
Estimated minimum sample size for two arms	64
Target recruitment size (accounting for 30% attrition)	80

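### The test that decides the primary outcome is not tied to reduction from baseline and, as worded, can average baseline into the medication effect

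*Protocol article*

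**What the plan says.** Under Outcomes {12}: "The primary outcome is the reduction in delirium severity as measured with the Memorial Delirium Assessment Scale (MDAS"). The same section gives a schedule of four measurements, the last at 72 h: "These data will be collected over four time-points: (i) baseline, (ii) 24 h after commencement". Sample size {14} takes 2 points as the smallest important difference and equates it with a 25% difference in the MDAS reduction. Objectives {7} describes a non-inferiority trial.

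Statistical methods {20a} takes changes in delirium severity across three successive 24-h periods as its subject and says that they "would be analysed using repeated-measures, between-factors ANOVA. If a statistically significant difference is found between medications", MDAS change at each time-point is then examined post hoc. For agitation on the RASS it says: "Similarly, the repeated-measures, between-factors ANOVA would be used to analyse the differences in scores".

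The section does not say whether the dependent variable is the MDAS score or its change from baseline. It does not say whether baseline is a level of the repeated factor, a reference or a covariate. It names no medication-by-time contrast.

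**The concern.** In a repeated-measures ANOVA with one between-patient factor, the between-medications effect compares the arms on each patient's average over the repeated measures. If baseline is one of those measures, the comparison is of average level and not of reduction. Baseline is taken before treatment and cannot carry a drug effect, so including it pulls the estimated difference towards zero. Change, which is the stated outcome, is reached only post hoc and only if the first test is significant.

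At stake is the match between the declared outcome and the statistic that decides the trial. Where the hope is to show that haloperidol is not unacceptably worse, shrinkage towards zero works in favour of the hoped-for answer.

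**Working it through.** **Inputs from the protocol article.** SD 7.64, difference 2 points, 32 per arm (Sample size {14}); measurements at baseline, 24, 48 and 72 h (Outcomes {12}).

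**Assumptions, not in the document.** Complete data; the same SD at each visit; the same correlation rho between any two visits, taken as 0.3, 0.5 or 0.7; the same drug difference at all three post-baseline visits. A half-SD difference, 7.64/2 = 3.82 points, is used beside the 2 points because power at 2 points is low under every analysis.

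**The plan's own figures.** The 25% follows from 2/8, with 8 the upper end of the 7–8 point reduction that the section cites. So the 2 points are a difference in reduction. The 32 per arm does not reproduce: the ordinary two-mean formula, 2 × 7.64² × (1.96 + 0.84)² / 2², gives about 230 per arm. That is a separate matter; 32 is used here only as the planned size.

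**Size of the effect.** Let d1, d2, d3 be the between-arm differences at 24, 48 and 72 h. Randomisation makes the expected baseline difference 0.

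- Four visits as levels: (0 + d1 + d2 + d3)/4.
- Mean change from baseline, or mean of the three post-baseline scores: (d1 + d2 + d3)/3.
- Ratio: (1/4)/(1/3) = 0.75, whatever the time course.
- With 2 points at each visit: 6/4 = 1.50 against 6/3 = 2.00. A simulation of 4,000 trials at rho 0.5 gave 1.52 for the four-visit level, 2.02 for the post-baseline level and 2.00 for mean change.

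**Three changes, each over one 24-h period.** Their average is (72 h minus baseline)/3, so the 24 h and 48 h values cancel. A 2-point difference appears as 2/3 = 0.67. Dividing an outcome by 3 leaves its F test unchanged, so this is a test of reduction to 72 h in other units.

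**Power.** Variance of each patient's summary, as a multiple of SD²:

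- four-visit level: (1 + 3rho)/4
- mean change: (1 + 2rho)/3 + 1 − 2rho = 4(1 − rho)/3
- post-baseline mean with baseline as covariate: (1 + 2rho)/3 − rho²

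The standard error of the between-arm difference is 7.64 × √multiple × √(2/32) = 1.91 × √multiple. At rho 0.5 and 3.82 points:

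- level: 0.75 × 3.82 = 2.865; SE 1.91 × √0.625 = 1.51; ratio 1.90
- mean change: SE 1.91 × √0.667 = 1.56; ratio 3.82/1.56 = 2.45
- covariate: SE 1.91 × √0.417 = 1.23; ratio 3.82/1.23 = 3.10

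Two-sided 5% power from the noncentral t with 62 degrees of freedom and these ratios as noncentrality:

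| True difference | rho | Four-visit level | Mean change | Baseline as covariate |
|---|---|---|---|---|
| 3.82 | 0.3 | 57% | 53% | 84% |
| 3.82 | 0.5 | 46% | 67% | 86% |
| 3.82 | 0.7 | 39% | 88% | 94% |
| 2 | 0.3 | 20% | 19% | 34% |
| 2 | 0.5 | 17% | 24% | 36% |
| 2 | 0.7 | 14% | 37% | 46% |

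With no true difference, the four-visit test rejected in 5.1–5.2% of 8,000 simulated trials per setting. The null error rate is sound; what suffers is the estimate and, at moderate or high correlation, the power.

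**The case against.** The strongest reply is that the sentence on the primary analysis takes changes in severity as its subject. Elsewhere, the abstract compares the arms at 24, 48 and 72 h and Trial design {8} lists only those three time-points. Collecting baseline does not make it an averaged outcome, since it is needed to compute change. An ANOVA of changes from baseline, or of the three post-baseline scores, estimates the full difference. All of this stands. A reader might infer that averaging baseline in is the plan's stated rule; the document does not say so.

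A reader might also infer more about the harm than the text supports:

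- **False non-inferiority.** Holding the diluted estimate against 2 points with a two-sided 95% interval would give a false claim in 4.3–5.8% of trials against a nominal 2.5% (simulated, rho 0.3 to 0.7). The statistical section contains no such interval or margin rule, so this is not a property of the plan.
- **The 0.67 figure.** This is mainly a rescaling, as shown above, and not a loss of sensitivity by dilution.
- **Uniform power loss.** At rho 0.3 or below, unadjusted mean change has no advantage over the level test.
- **The same quarter for RASS.** Outcomes {12} lists four time-points, but caregivers chart RASS every 6 h. With baseline and 72/6 = 12 later readings the factor would be 12/13 = 0.92, so the size is not fixed.

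It can also be said that the handling of baseline belongs in a statistical analysis plan. That would answer a section silent on the test. This one names the ANOVA, names the effect that decides, and makes change at each time-point conditional on it. Nor do the words about changes over three periods settle the matter: they fit changes from baseline, changes within each period, or a general description of a four-visit analysis. The sample size uses a score SD and not a change SD ("the mean scores from the Memorial Delirium Assessment Scale for patients with delirium is roughly 18 (SD = 7.64"), which suits an analysis of scores.

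**Conclusion.** The concern holds as a mismatch left open by the wording. The outcome and the 2-point difference are reductions; the decision rests on a between-medications effect that is not tied to reduction. On one natural reading, with four visits as levels, that effect is exactly three quarters of the mean post-baseline difference, so 2 points becomes 1.5. On a change-from-baseline or post-baseline-only reading there is no dilution. The three-quarters figure needs only equal expected baselines.

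The power figures rest on complete data, equal SDs and an assumed common correlation: a clear loss against unadjusted mean change at 0.5 and 0.7, none at 0.3. With a non-inferiority aim the direction of the bias is the unhelpful one, so the wording should be settled before analysis.

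**What to change.** In Statistical methods {20a}:

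- Name as the decision statistic the between-arm difference in MDAS change from baseline over 24, 48 and 72 h. Choose one form in advance: the baseline-versus-post-baseline by medication contrast, or the post-baseline mean with baseline as covariate.
- State that baseline is not averaged into the medication effect.
- Report the between-arm difference in change at each time-point whatever the overall test shows.
- State the same baseline-referenced contrast for RASS, and which RASS readings enter it.

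The cost is wording only; no new data, visits or patients are needed. The small downside is that at a correlation of about 0.3 or less an unadjusted change score is no more powerful than the main effect. Using baseline as covariate avoids this.

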A recent Cochrane systematic review evaluating the effectiveness and safety of drug therapies to manage delirium symptoms in terminally ill adults has only found four clinical studies that included haloperidol and olanzapine, with high risks of bias and low to very low quality of evidence. Due to the absence of evidence from robust clinical trials, current recommendations are based on consensus or expert opinion, and clinical experience in the care of patients at the end of life [3]. Given these considerations, we believe there is immense value in comparing the therapeutic effects of haloperidol versus olanzapine within the hospice home care setting at the end of life; other researchers have encouraged this investigation to be pursued [4].

Hence, we propose an open-label randomised clinical trial to compare the effects of haloperidol and olanzapine in the management of terminal delirium in home hospice patients who are imminently dying. Key outcome measures are the reduction of delirium symptoms and the reduction of agitation. Secondary outcome is the adverse effect burden on patients.

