### Objectives {7}

This study is a non-inferiority trial that aims to compare the effect of Oral Transmucosal (OT) haloperidol and olanzapine in the management of terminal delirium in dying patients receiving home hospice care. The study’s secondary objective is to record the frequency and severity of toxicity from treatment. It is hypothesised that OT Haloperidol will reduce the severity of agitation and of terminal delirium as effectively as OT olanzapine, i.e. Haloperidol will not perform “unacceptably worse” than olanzapine.

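### The trial declares a non-inferiority objective, but its primary analysis is an ANOVA of no difference and no non-inferiority margin is declared or used

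*Protocol article*

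**What the plan says.** Objectives {7} is explicit about the design: "This study is a non-inferiority trial that aims to compare the effect of Oral Transmucosal (OT) haloperidol and olanzapine". The hypothesis has one direction: "Haloperidol will not perform “unacceptably worse” than olanzapine".

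Statistical methods {20a} fixes the primary analysis. Change in delirium severity, "as measured with the MDAS, would be analysed using repeated-measures, between-factors ANOVA". The only sentence on what follows from the result is: "If a statistically significant difference is found between medications, post hoc analysis will be conducted". Agitation (RASS) is analysed the same way.

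Sample size {14} supplies the only quantity that could act as a margin: "we estimate 2 points to be the minimal important difference between haloperidol and olanzapine". Table 3 enters it as the effect size, with SD 7.64, power 0.80 and alpha 0.05, and arrives at 32 per arm.

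The outcome hierarchy varies. Outcomes {12} names MDAS alone as primary and puts RASS among the secondary outcomes. Background {6a} says: "Key outcome measures are the reduction of delirium symptoms and the reduction of agitation". The hypothesis in {7} covers agitation and delirium together, and {20a} speaks of a first primary outcome, then of a second outcome.

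**The concern.** A non-inferiority claim needs a margin and a test or interval that rules out a deficit of that size. The ANOVA tests the null hypothesis of no difference, in either direction, and contains no margin. A significant result in favour of olanzapine counts against the hypothesis. A significant result in favour of haloperidol would support it, but only by showing superiority, which is not the aim. In the remaining case, non-significance, the data may still be compatible with a large deficit.

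The incentive also runs the wrong way. The smaller or noisier the trial, the more likely a non-significant F test becomes. Early deaths and discontinuations are expected here (sections {11b} and {18b}), so this is a practical matter.

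**Working it through.** **The two sections side by side.** The question in {7} is whether a deficit large enough to be unacceptable can be excluded. The question answered in {20a} is whether the drugs differ at all. The 2 points in {14} appear in neither, and no other section gives a margin or a confidence-interval criterion for MDAS or RASS.

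**Inputs.** From {14}: 32 per arm, SD 7.64, difference 2, power 0.80, alpha 0.05. Assumed because not stated: alpha is two-sided; MDAS values at all time points share the same SD and a common within-patient correlation ρ, shown over a range; all 32 per arm contribute every visit.

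**The plan's own figure.** For one visit, n per arm = 2 × [7.64 × (1.960 + 0.842) / 2]² = 229.1, so 230, not 32. For the mean of three post-baseline visits adjusted for baseline, multiply by (1 + 2ρ)/3 − ρ²: this gives 96, 72 and 29 per arm at ρ = 0.5, 0.7 and 0.9. Under this layout 32 per arm needs ρ near 0.9. The stated power therefore depends on a quantity that the article does not give, which is why a range is shown.

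**Chance of a non-significant result, and power of a proper test.** The variance factor f is 1 for one visit, (1 + 2ρ)/3 for the unadjusted mean of three visits, and (1 + 2ρ)/3 − ρ² with baseline adjustment. SE = 7.64 × √(2f/32). Probabilities come from the noncentral t with 62 degrees of freedom and noncentrality (true difference)/SE. The last column is the power to put the upper 95% limit below 2 points when the drugs are truly equal.

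| Analysis | f | SE | 95% CI half-width | Non-significant if truly 2 worse | Non-significant if truly 4 worse | Power for non-inferiority at 2 points |
|---|---|---|---|---|---|---|
| One visit | 1 | 1.91 | 3.82 | 82% | 46% | 18% |
| Mean of 3 visits, ρ 0.5 | 0.667 | 1.56 | 3.12 | 76% | 29% | 24% |
| Baseline-adjusted, ρ 0.5 | 0.417 | 1.23 | 2.46 | 64% | 11% | 36% |
| Baseline-adjusted, ρ 0.7 | 0.310 | 1.06 | 2.13 | 54% | 4% | 46% |
| Baseline-adjusted, ρ 0.9 | 0.123 | 0.67 | 1.34 | 17% | under 1% | 83% |

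If the stated 80% power at 2 points is taken at face value, a true 2-point deficit is non-significant in 100% − 80% = 20% of trials. Under a rule that needs the upper limit of a two-sided 95% interval to lie below the margin, a true deficit equal to the margin leads to a false claim in 2.5%, whatever the sample size or correlation.

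**The case against.** Four points deserve weight.

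- A reader might infer that the plan commits the trial to reporting a non-significant ANOVA as equal effectiveness. It does not say so. The significance condition in {20a} gates only the analyses by time point; it does not state when the hypothesis in {7} is accepted. What stands is narrower: an equality test is fixed, and no criterion for the declared objective is given.
- A reader might take 2 points as the declared non-inferiority margin. Section {14} calls it a minimal important difference and uses it as an effect size. It is the only candidate in the document, but it has not been adopted or justified as a margin.
- The error rates depend on assumptions. That a non-significant result is likely at a 2-point deficit holds at low to moderate correlation, not at 0.9 and not if the stated power is right. The figures for a 4-point deficit are more fragile still. The logical defect needs none of them: even 20% is eight times 2.5%.
- An analysis plan that is not shown may exist, and a repeated-measures model can yield a between-drug contrast with an interval. An article may leave such detail to it. But {20a} names the test and what follows from significance, so the conflict lies in what is stated, not in what is left out.

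The varying outcome hierarchy is a lesser matter, since Outcomes {12} is clear. It belongs here only because a non-inferiority claim must say on which scale it is made.

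**Conclusion.** The point holds as a contradiction between Objectives {7} and Statistical methods {20a}. As written, the plan has no valid route to its hypothesis short of showing haloperidol superior, and a non-significant ANOVA would not establish it.

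With 32 per arm, SD 7.64 and two-sided 0.05, a true 2-point deficit would go undetected in between 17% and 82% of trials, depending on the analysis and on a correlation that the article does not state, or in 20% if its power figure is accepted. The benchmark is 2.5%. The conclusion rests on the mismatch between objective and test; the percentages show its size under the stated assumptions. It should be corrected before analysis.

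**What to change.** 1. Declare a non-inferiority margin for MDAS and justify it. If the 2-point figure is chosen, say so and say why a deficit just under 2 points would be acceptable.
2. Replace the decision rule in {20a}. Estimate the haloperidol-minus-olanzapine difference in MDAS score, adjusted for baseline, for one named contrast (for example the average over 24, 48 and 72 h), with a two-sided 95% confidence interval. Claim non-inferiority only if the upper limit lies below the margin.
3. State that a non-significant difference is not non-inferiority.
4. Report the differences by visit with confidence intervals, without a significance gate.
5. Align {6a}, {7} and {20a} with {12}: MDAS primary, RASS secondary.
6. Restate the power for this test, with the assumed correlation and the sidedness of alpha.

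Items 2 to 5 cost only wording, and item 1 a reasoned choice. Item 6 may cost more. With 32 per arm and a 2-point margin, power when the drugs are truly equal is about 18% (one visit), 24% (three-visit mean, ρ 0.5), or 36%, 46% and 83% (baseline-adjusted, ρ 0.5, 0.7 and 0.9). Unless a correlation near 0.9 can be defended, the corrected trial would more likely than not be inconclusive. The sponsor would then need to revisit the sample size or restate the objective as estimating the difference with its interval.

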**Methods:**

Eighty patients with a prognosis of 7 days or less will be recruited for an open-label randomised control trial. The two arms compare oral-transmucosal haloperidol 2.5 mg vs olanzapine 5 mg over 72 h. The severity of agitation, delirium and toxicities of treatments will be compared at the 24th, 48th and 72nd hour after drug administration.

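### MDAS is to be analysed by time-point only after a significant overall drug difference, although the abstract promises the 24, 48 and 72 h comparison without condition and the trial is declared non-inferiority

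*Protocol article*

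**What the plan says.** All references are to the protocol article.

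- **Abstract, Methods:** "The severity of agitation, delirium and toxicities of treatments will be compared at the 24th, 48th and 72nd hour after drug administration". No condition is attached.
- **Objectives {7}:** "This study is a non-inferiority trial", with the hypothesis that "OT Haloperidol will reduce the severity of agitation and of terminal delirium as effectively as OT olanzapine".
- **Outcomes {12}:** "These data will be collected over four time-points", namely baseline, 24 h, 48 h and 72 h. MDAS is the primary outcome.
- **Statistical methods {20a}:** changes in MDAS severity "would be analysed using repeated-measures, between-factors ANOVA". Then: "If a statistically significant difference is found between medications, post hoc analysis will be conducted" on the MDAS change at each time-point. For RASS the section says only that the same type of ANOVA will be used; no condition is written for it.
- **Additional analyses {20b}:** marked as not applicable. No other section supplies an unconditional comparison of MDAS by time-point.

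**The concern.** The abstract and the statistical methods section cannot both be followed when the overall test is non-significant. One promises the comparison at three hours; the other runs it only after significance.

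The rule also runs against the trial's aim. A non-inferiority claim rests on showing how large a disadvantage of haloperidol remains compatible with the data. The visit-level differences with their intervals are part of that evidence, and they are most useful when the overall test is not significant. A rule that opens them only after a significant difference suits a search for differences.

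In the other direction, estimates seen only because a related test crossed 5% are too large on average. A reader would meet the 24, 48 and 72 h differences mainly in trials where chance had pushed them up.

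**Working it through.** **1. The two statements side by side.** Abstract: comparison at 24, 48 and 72 h, always. Section {20a}: MDAS analysis at each time-point only after significance. With a non-significant overall test, the first requires the comparison and the second does not provide it.

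**2. Inputs.** From Table 3: SD 7.64, difference 2 points, 32 per arm, alpha 0.05. Assumed, because the protocol gives no value: within-patient correlation ρ of 0.3, 0.5 or 0.7 (equal between all visits), a two-sided test, and no missing visits. For this step the condition is read as the drug main effect over the three post-baseline visits.

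The protocol gives no figure for how often the condition would be met, so there is none to reproduce. The 32 per arm is taken as printed. It does not follow from the simple two-group formula: 2 × (1.960 + 0.842)² × 7.64² / 2² = 229.1, or 230 per arm. That is a separate matter, but it explains why power is low below.

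**3. Formulas.**
- Variance of a patient's three-visit mean: 7.64² × (1 + 2ρ) / 3.
- SE of the between-arm difference: √(2 × variance / 32).
- Chance that the condition is met for true difference δ: P(|estimate| > 1.96 × SE).
- Mean estimate given significance in the true direction: δ + SE × φ(a) / (1 − Φ(a)), with a = (1.96 × SE − δ) / SE.

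**4. Results.**

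| | ρ = 0.3 | ρ = 0.5 | ρ = 0.7 |
|---|---|---|---|
| Variance of three-visit mean | 31.13 | 38.91 | 46.70 |
| SE of difference | 1.39 | 1.56 | 1.71 |
| Smallest significant estimate (points) | 2.73 | 3.06 | 3.35 |
| Condition met, δ = 0 | 5% | 5% | 5% |
| Condition met, δ = 2 | 30% | 25% | 22% |
| Mean estimate if met, δ = 2 | 3.62 | 3.99 | 4.32 |
| Condition met, δ = 4 | 82% | 73% | 65% |
| Mean estimate if met, δ = 4 | 4.45 | 4.71 | 4.98 |

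So with equal drugs about 95% of trials give no time-point comparison. At δ = 2 the reported difference averages about twice the truth. At δ = 4 the inflation is 11%, 18% and 24%; at δ = 6 the mean estimate is 6.04–6.22, under 4% too high.

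**5. Check by simulation** (10,000 trials per setting, reading the 72 h estimate only when the overall test was significant, and analysing either post-baseline scores or change from baseline). At δ = 0 the condition was met in 4.6–5.4% of trials. At δ = 2 it was met in 18–37% with 32 per arm (mean 72 h estimate 3.2–4.5 points) and in 22–45% with 40 per arm (2.9–4.1 points).

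**6. Which ANOVA term?** Suppose the true difference is 2 points at 24 h and zero at the other visits.
- Main effect over three visits: the average is 2/3 = 0.67 points, and the condition is met in 7.7%, 7.1% and 6.8% of trials.
- Drug-by-time term over four time-points: the noncentrality is (32/2) × Σ(d − mean d)² / (7.64² × (1 − ρ)). With differences 0, 2, 0, 0 the sum is 3, so the noncentrality is 1.18, 1.64 and 2.74 on 3 and 186 degrees of freedom. The condition is met in 13%, 16% and 25% of trials.

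A crossing pattern (+4, 0, −4 points) meets the condition in about 5% of trials under the main effect (simulated at ρ = 0.5), but in 85% to 99.8% under the drug-by-time term. The answer turns on a choice that {20a} does not state.

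**The case against.** **Testing individual visits only after a significant overall test is a conventional guard against multiplicity.** True, but it guards tests. Supporting estimates with intervals need no such guard, and reporting them leaves the error rate of the primary test unchanged.

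**The abstract may only be naming the assessment times.** Its verb is that severity will be compared at those hours, which is more than saying when data are collected. The tension remains, though it rests on one sentence of an abstract.

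**The figures mainly show low power.** This stands in part. The 22–30% and the twofold inflation arise because 32 per arm is few for a 2-point difference. The selection bias is real at any effect size but becomes small as the true effect grows.

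**The deeper problem is a difference test in a non-inferiority trial.** That is fair, and the change proposed here does not cure it.

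A reader might also infer more than the protocol supports:
- *A late or fading effect will be averaged away.* This holds only if the main effect is the condition. Under the drug-by-time term such patterns are what the test looks for.
- *No MDAS figures by visit will ever appear.* The text makes the post hoc analysis conditional. It does not forbid descriptive means, and equal drugs still give significance in about 5% of trials. A non-inferior result can also coexist with a significant difference, for instance one favouring haloperidol.
- *Every published time-point difference will be exaggerated.* The bias is an average, not a property of each estimate.
- *RASS is subject to the same condition.* None is written for it.
- *The 24 h result is the one most patients reach alive.* Plausible given the short prognosis required for entry, but the protocol gives no survival figures.

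**Conclusion.** The point holds in limited form. The statistical methods section makes the MDAS time-point analysis depend on significance, the abstract promises it regardless, and no other section fills the gap. Under the trial's own hypothesis the usual outcome is one in which no time-point comparison is planned. When it is run, the estimates are biased away from zero on average.

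The bias is about twofold at the protocol's 2-point difference and modest at 4 points. Those figures depend on the assumed correlation, complete data, a two-sided 5% test and the main-effect reading of the condition. The contradiction and the selection by significance depend on none of these. The primary test itself is unaffected, so this is a change that should be made but does not threaten the trial's validity.

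**What to change.** In {20a}, delete the condition and replace the sentence with one to this effect: from the same repeated-measures model, including a medication-by-time term, the between-arm difference in MDAS change from baseline will be reported with a 95% confidence interval at 24, 48 and 72 h whatever the overall result, as supporting estimates. With that label no multiplicity adjustment is needed.

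Reporting RASS in the same way would match the abstract, which promises agitation at the same hours. That is for consistency only, since no condition is stated for RASS.

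The cost is one sentence in the analysis section, with no new data, visits or patients.
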